##### Primary outcome (compulsion duration)

Following procedures outlined for this outcome in Phase 1, a linear regression model will assess whether compulsion duration differs by treatment group. A linear regression model will also be used with the outcome of interest being the percent change in OCD symptom severity (C/YBOCS) pre- to post-treatment. The primary predictor will be a group indicator for sham vs active rTMS. Compulsion duration and its interaction with the group indicator will be included as potential mediators for the dependent variable. Total exposure duration will be a covariate in both analyses.

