### Trial design {8}

Both phases are randomized, sham-controlled, double-masked, parallel-group, superiority trials. Phase 1 is a three-arm trial (sham, cTBS to pSMA, or iTBS to dlPFC; *n* = 20 per group), and phase 2 is a two-arm trial (sham or active stimulation; *n* = 30 per group; Fig. 1). Randomization in both phases will be blocked on site (Brown University or University of Minnesota) and symptom severity (Children’s or adult Yale-Brown Obsessive Compulsive Scale score above or below 32, indicating the cutoff for “extreme” symptoms). Participants have a 2 in 3 chance of being assigned to an active TMS treatment arm.

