Primary outcomes focus on neural change and will be indexed by within-subject (pre- to post-treatment) and between-subject (iTBS vs. sham; cTBS vs. sham) change in fMRI-measured RSFC between the targeted network (pSMA-DLS for cTBS arm, dlPFC-DMS for iTBS arm). We will also examine several other outcomes. First, we will evaluate between-subject differences in compulsions during ERP (rate per session as observed by independent raters using EPCS). We will assess safety at baseline, post-treatment, daily treatment sessions, and 1-month follow-ups using the staff-administered Adverse Events Questionnaire (TMS AEQ), aggregated as the number of treatment-related adverse events and tolerability ratings of side effects. We will assess feasibility at post-treatment, based on treatment completion rate (percent of participants completing ≥ 80% of treatment sessions).

#### Phase 2

The primary outcomes are neural change (RSFC in the targeted circuit as in Phase 1) and change in compulsion rate (rate per session as in Phase 1). These will be indexed by within-subject (pre- to post-treatment) and between-subject (active vs. sham) change. We will also examine whether changes in neural and behavioral outcomes mediate change in OCD symptom severity (percent change in C/YBOCS total score from pre- to post-treatment). Secondary analyses will examine (1) the relationship between pre-treatment clinical measures and OCD symptom change, and (2) subgroup effects in primary outcomes, and (3) durability of change in primary outcomes through 1-month follow-up.

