### Assignment of interventions: allocation

#### Sequence generation {16a}

Block randomization, stratified on site (Brown or UMN) and baseline OCD severity (C/YBOCS total < 32 vs. > = 32), will be performed using the blockrand package in R [37].

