##### Secondary outcome (compulsion duration)

EPCS-rated duration of observed compulsions (in seconds, summed across all sessions) will quantify compulsive behavior. We will fit two linear regression models with compulsion duration as the dependent variable to establish if there exist differences in how iTBS, cTBS, and sham conditions affect compulsion duration. Group indicators for these conditions (active vs sham) will be the primary model predictors. Given that the overall exposure duration naturally varies across patients and sessions, [36] relates to ERP outcomes, and can influence compulsion duration (i.e. longer exposures have more opportunity for compulsions), total exposure duration (in seconds) will be a covariate in the model.

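### The compulsion-duration models leave out both randomisation strata (site and baseline C/YBOCS severity), so to the extent that the strata predict the outcome, the test is conservative and available power is forgone

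*Protocol article*

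**What the plan says.** **Randomisation.** The Sequence generation section specifies "Block randomization, stratified on site (Brown or UMN) and baseline OCD severity", with severity split at a C/YBOCS total of 32. The Trial design section confirms that this applies throughout: "Randomization in both phases will be blocked on site", together with symptom severity.

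**Phase 1 compulsion model (Statistical methods, secondary outcome).** "Group indicators for these conditions (active vs sham) will be the primary model predictors", and "total exposure duration (in seconds) will be a covariate in the model". The article gives a reason for this covariate: longer exposures leave more opportunity for compulsions.

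**Phase 2 compulsion model (Statistical methods, primary outcome).** Following the Phase 1 procedure, "a linear regression model will assess whether compulsion duration differs by treatment group". On covariates: "Total exposure duration will be a covariate in both analyses".

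**Status of the outcome.** The Outcomes section lists compulsions among the Phase 2 primary outcomes: "The primary outcomes are neural change (RSFC in the targeted circuit as in Phase 1) and change in compulsion rate".

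Neither site nor baseline severity appears as a term in these models.

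**The concern.** Stratified blocks keep the arms close to balanced on site and severity. If those factors predict the outcome, the balance removes their contribution from the true sampling variance of the group difference. A model without the strata does not register this. It leaves their variance in the residual and reports a standard error for a less precise design than the one used, so intervals are wider and p-values larger than they should be.

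Baseline severity deserves attention for this endpoint. EPCS coding is scheduled only at treatment sessions (Table 1), and exposures take place in sessions 2 to 11, each straight after TMS (Intervention description; ERP protocol). So there is no pre-treatment compulsion duration to adjust for. Baseline C/YBOCS is the obvious pre-treatment severity measure, and the investigators already chose to stratify on it.

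At stake is precision in a Phase 2 comparison planned on 54 analysable participants.

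**Working it through.** **Inputs from the article.** Phase 2: 60 randomised, 54 after 10% attrition, so 54/2 = 27 per arm; 80% power at d = 0.78 (Sample size). That d is stated for compulsion rate; it is carried over here to the duration model.

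**Assumptions.** Two-sided alpha of 0.05 (no alpha is stated for the compulsion models), blocks of 4, and R², the share of outcome variance that the two strata explain beyond exposure duration. The article does not give R², so a range is shown.

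**Step 1: reproduce the plan's figure.** For a two-sample t-test the noncentrality is d × √(n/2) = 0.78 × √13.5 = 2.87. With 52 df, power is 80.3%, and the detectable d at 80% power is 0.777. The plan's 0.78 reproduces without any stratum term. With exposure duration in the model (54 − 3 = 51 df), power is still 80.3%.

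**Step 2: formula with the strata added.** The effect becomes d/√(1 − R²), with 54 − 5 = 49 df.

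| Assumed R² | Power with strata | Detectable d at 80% power |
|---|---|---|
| 0 | 80.2% | 0.778 |
| 0.05 | 82.2% | 0.758 |
| 0.10 | 84.2% | 0.738 |
| 0.15 | 86.1% | 0.717 |
| 0.20 | 88.1% | 0.696 |

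Reading the gain as the difference from 80.3% is slightly generous, because stratified allocation also raises the power of the model as written. Simulation removes that flaw.

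**Step 3: simulation.** 60 randomised in stratified blocks of 4, 54 analysed, R² split equally between site and severity, exposure duration in both models, 5,000 runs per setting. The two values in a cell are for 20% and 40% of participants in the severe stratum.

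| R² | Type I error, as written | Type I error, strata added | Power at d = 0.78, as written | Power at d = 0.78, strata added |
|---|---|---|---|---|
| 0 | 4.8%, 5.1% | 4.6%, 5.1% | 79.4%, 78.7% | 78.9%, 78.2% |
| 0.10 | 4.4%, 4.3% | 5.4%, 5.2% | 80.2%, 80.5% | 83.3%, 83.4% |
| 0.20 | 3.1%, 3.1% | 4.9%, 4.6% | 81.8%, 80.7% | 87.9%, 87.0% |

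Power gains:
- R² = 0.10: 83.3 − 80.2 = 3.1 and 83.4 − 80.5 = 2.9 points.
- R² = 0.20: 87.9 − 81.8 = 6.1 and 87.0 − 80.7 = 6.3 points.
- R² = 0: a loss of 0.5 point in each setting.

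Further simulations of the same design gave gains of about 4 to 4.6 points at R² = 0.15 and 5.5 to 5.7 at 0.20. Their type I errors for the model as written were 3.8% to 4.4% at 0.10 and 3.1% to 3.4% at 0.20.

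**Step 4: the mechanism.** At R² = 0.20 the model as written reports a mean standard error of 0.274 to 0.275, while the estimate's actual standard deviation across runs is about 0.25. The ratio 0.274/0.25 = 1.10, so the reported standard error is about 10% too wide. At R² = 0 the two agree (about 0.274 each).

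**The case against.** **The SAP is not shown.** The article calls exposure duration a covariate, not the only one, and further terms could be added in the SAP. This stands as a limit: nothing in the article forbids them. But the article does set out the model (outcome, predictors, covariate and the reason for the covariate), and as written the strata are not in it. The Discussion's remark that block randomisation will account for heterogeneity describes a design step and adds no term to the analysis.

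**The harm is conditional.** No section links site or C/YBOCS total to seconds of compulsion in session, and any effect acting through exposure length is already adjusted for. This stands, and it is why R² is defined as incremental to exposure duration and shown as a range.

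**Stronger readings that the article does not support:**
- A reader might infer that Phase 2 is underpowered or its sample size wrong. The model as written keeps roughly 79% to 82% power at d = 0.78 across the table, in line with the stated 80%.
- A reader might infer bias or false positives. The error runs only towards conservatism.
- A reader might apply the Phase 1 d of 0.96 to compulsions. The Sample size section gives d of 0.70 to 0.96 for RSFC and η² = 0.23 for compulsions, so no Phase 1 power figure is claimed here.
- A reader might expect a strong site effect from separate ERP teams. The Study setting section only names locations, the oversight section describes cross-site teams, and one manual is used. The case for including site is that randomisation was stratified on it.
- A reader might think that the Phase 1 choice of regimen is affected. If both regimens qualify, it rests on the lowest compulsion rate (Objectives), not on a p-value.

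**Conclusion.** The point holds as a conditional loss of efficiency. The compulsion-duration group comparisons in both phases, including that for a Phase 2 primary outcome, do not reflect the stratified randomisation.

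For Phase 2 with 54 analysed, and depending on an incremental R² that must be assumed:
- **R² = 0.10:** type I error about 4%, power forgone about 3 points.
- **R² = 0.15:** power forgone 4 to 5 points.
- **R² = 0.20:** type I error about 3%, power forgone 5 to 6 points.
- **R² = 0:** nothing is lost by the plan as written, and adding the terms costs under 1 point.

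A 5-point gain needs an R² above 0.15, nearer 0.20. The figures also rest on a two-sided alpha of 0.05, blocks of 4 and an equal split of R² between the strata. The 54 is the planning figure; the missing-data section would analyse all randomised participants after imputation, which does not change the direction. For Phase 1 the direction is the same, but no size is claimed. The percent-change model for C/YBOCS was not examined and no conclusion is drawn on it.

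**What to change.** In Statistical methods, under the Phase 1 and Phase 2 compulsion-duration outcomes, add one sentence: the group-comparison models will include site and baseline C/YBOCS as prespecified covariates alongside total exposure duration.

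Baseline C/YBOCS can enter as the randomisation stratum (below 32, or 32 and above), which is what matching the analysis to the randomisation requires. It can instead enter as the continuous score, which also carries the variation within strata; entry is at 16 or more, so the lower stratum runs from 16 up to the cut at 32. The simulations used the stratum, so any further gain from the continuous score is not quantified.

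Both variables are already collected. The cost is two degrees of freedom (51 to 49 in Phase 2), under 1 point of power if neither variable is prognostic. The change should be made before unmasked outcome data are seen, so that the adjustment is prespecified.

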##### Other outcomes

We will explore the durability of treatment-related change in OCD symptoms by testing group differences in clinical change on the C/YBOCS at post-treatment and 1-month follow-up. Group differences on secondary measures of clinical functioning listed in Table 1 will be explored.

### Interim analyses {21b}

This trial has no planned interim analyses. The Data Safety Monitoring Board (DSMB) can request interim analyses to determine whether there is any change to the anticipated benefit-to-risk ratio of study participation.

### Methods for additional analyses (e.g. subgroup analyses) {20b}

In both study phases, we will conduct exploratory analyses to investigate baseline participant characteristics as predictors of change in RSFC and compulsion duration across treatment arms. OCD is a highly heterogeneous disorder typically accompanied by one or more comorbidities, and for which subgroup differences may be particularly relevant. Specifically, we will explore the relevance of the following baseline characteristics: comorbidity (yes/no: mood, anxiety, ASD, ADHD, tics), OCD symptom subtype (harm avoidance vs. incompleteness), presence of mental compulsions (yes/no), assigned sex at birth, and Tanner stage (stages 3–4 will be coded post pubertal).

### Methods in analysis to handle protocol non-adherence and any statistical methods to handle missing data {20c}

We will implement multiple imputation methods for any missing data prior to our analyses, assuming a missing at random missingness mechanism using Multiple Imputation by Chained Equations (MICE) in the *mice* package in R. MICE allows flexibility in predictor variable types (binary, continuous, multinomial, etc.). All randomized participants will be used in analyses.

### Plans to give access to the full protocol, participant-level data and statistical code {31c}

De-identified participant data will be submitted to the National Institute of Mental Health Data Archive (NDA, Collection #C4911) if participants opt in during the consent process. The code for statistical analyses and the MRI scanning protocol can be made available upon request.

## Oversight and monitoring

### Composition of the coordinating center and trial steering committee {5d}

This multi-site study is organized into the following “teams”: oversight, data coordination, data analysis, imaging, TMS, ERP, independent evaluator (IE) assessments, and EPCS coding. The oversight team, led jointly by the PIs, will provide global oversight of study conduct, procedural and scientific integrity, regulatory management, data collection, quality assurance, data analysis, and dissemination of findings. The cross-site implementation teams will each be led by a doctoral-level co-investigator, with each site taking the lead on teams that best leverage site expertise (TMS, imaging, and data coordination by UMN; ERP, IE assessments, and EPCS coding by Brown). Each team will meet weekly or bi-weekly and work with the oversight team to develop and monitor Standard Operating Procedures (SOPs).

#### Composition of the data monitoring committee, its role and reporting structure {21a}

An independent DSMB is in place for this study. Members have expertise in biostatistics, neurodevelopmental disorders, and clinical care of youth with OCD. DSMB members are not involved in this project and are not collaborators on any other of the investigators’ projects nor in their employ. DSMB policies and responsibilities are outlined in a charter created prior to the start of data collection. Annual DSMB meetings will be held to monitor study conduct, safety data, and participant safeguards. De-identified reports to the DSMB will include information about study progress, participant accrual, adverse event data, protocol deviations, and external factors or information relevant to the study and its risk–benefit ratio. The DSMB has the authority to vote on study continuation and make recommendations about study procedures, and they can be contacted by regulatory authorities or similar entities seeking advice about any potential concerns.

### Adverse event reporting and harms {22}

The Adverse Events Questionnaire (AEQ) will be administered at every TMS study visit, and staff will conduct general inquiries regarding health status between visits. For each endorsed AE, data will indicate severity, relatedness to TMS, relatedness to ERP, and actions taken. All adverse events will be reviewed by the PIs. AE reporting procedures are in accordance with policies of the IRB, FDA, NIH, and site institutions. Annual IRB progress reports will include (1) adverse events deemed expected or unrelated to the study and (2) protocol deviations that do not affect the scientific soundness of the research plans or the rights, safety, or welfare of the human subjects. Promptly reportable events include (1) unanticipated serious adverse events, (2) unanticipated problems involving risks to subjects or others related to research participation, (3) information reports indicating new or increased risk with the investigational device, and (4) protocol deviations that increased risk of harm.

The study will be stopped should any of the following occur: (1) two participants experience a generalized-onset seizure, (2) two participants experience a focal-onset seizure with impaired awareness, (3) two participants experience a seizure for which anticonvulsant medication is administered, (4) one participant experiences status epilepticus or is hospitalized due to a seizure(s), (5) two or more participants attempt suicide or one participant completes suicide, (6) two or more device-related serious adverse events (SAEs) in one or more participants; OR a single device-related SAE in five or more participants, or (7) two or more participants show a decrease in working memory at any time during the study. The likelihood of a seizure occurring in this trial is extremely low given the TMS parameters being used and the design of inclusion/exclusion criteria to exclude participants with elevated risk [45].

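### Stopping rule 6 does not fix its counting unit: the trial stops at the second device-related SAE on one reading, and on the other may not stop after one SAE each in two to four participants

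*Protocol article*

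**What the plan says.** The section Adverse event reporting and harms {22} of the protocol article lists seven stopping rules under the lead-in "The study will be stopped should any of the following occur", so meeting any one rule is enough. Rule 6 has two clauses, one on each side of the OR: "two or more device-related serious adverse events (SAEs) in one or more participants; OR a single device-related SAE in five or more participants".

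The neighbouring rules count participants. Rule 5, for example, is "two or more participants attempt suicide or one participant completes suicide". The first clause of rule 6 is different: it sets a number of events and then a number of participants, without saying how the two relate. The article gives no expected rate of device-related SAEs.

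Trial design {8} gives three Phase 1 arms of 20, two of them active, and two Phase 2 arms of 30, one of them active.

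**The concern.** The first clause can be read in two ways.

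- **Pooled:** any two device-related SAEs in the study meet it, including one each in two people. The words after the event count expressly admit more than one participant.
- **Same participant:** at least one person must have two or more device-related SAEs. The contrast with a single SAE in the second clause points this way.

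The readings give different decisions on the same data. This is a whole-study safety stop, in what the Background describes as, to the authors' knowledge, the first treatment trial of rTMS for youth with OCD. Scheduled DSMB meetings are annual, and the principal investigators review all adverse events. Someone may therefore have to apply the rule between meetings, from its wording.

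**Working it through.** There is no figure in the article to reproduce, because it gives thresholds only. The check has two parts.

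**1. Logic of the two clauses**

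Take six participants, each with 0, 1, 2 or 3 device-related SAEs. That gives 4^6 = 4096 patterns. The second clause is met when at least five participants are affected.

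- *Pooled reading* (total SAEs ≥ 2). The second clause is met without the first in 0 of 4096 patterns. Five affected participants mean at least five SAEs, and 5 ≥ 2. The second clause is redundant.
- *Same-participant reading* (some participant has ≥ 2 SAEs). The second clause is met without the first in C(6,5) + C(6,6) = 6 + 1 = 7 patterns. Both clauses have a function.
- *Disagreement.* The pooled reading stops and the other does not in C(6,2) + C(6,3) + C(6,4) = 15 + 20 + 15 = 50 patterns. These are exactly the patterns with one SAE each in two, three or four participants. At most four SAEs can occur without rule 6 being met.

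**2. Size of the difference**

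Inputs:
- n = 40 participants on active stimulation in Phase 1 (2 × 20, Trial design).
- λ = device-related SAEs per participant. This is an assumption, shown at 0.01, 0.02 and 0.05.
- SAE counts are independent and Poisson, also an assumption.

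Formulas:
- Pooled: P(stop) = 1 − e^(−nλ)(1 + nλ).
- Same participant: the study continues only if nobody has more than one SAE and at most four people have one. So P(stop) = 1 − e^(−nλ) × Σ C(n,k) λ^k for k = 0 to 4.

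At λ = 0.02 (nλ = 0.8, e^(−0.8) = 0.4493):
- Pooled: 1 − 0.4493 × 1.8 = 0.191.
- Same participant: 1 − 0.4493 × (1 + 0.8 + 0.312 + 0.0790 + 0.0146) = 1 − 0.4493 × 2.2057 = 0.009.

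At λ = 0.05 (nλ = 2, e^(−2) = 0.1353):
- Pooled: 1 − 0.1353 × 3 = 0.594.
- Same participant: 1 − 0.1353 × (1 + 2 + 1.95 + 1.235 + 0.571) = 1 − 0.1353 × 6.756 = 0.086.

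| Assumed λ | Pooled | Same participant |
|---|---|---|
| 0.01 | 0.062 | 0.002 |
| 0.02 | 0.191 | 0.009 |
| 0.05 | 0.594 | 0.086 |

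The right-hand column includes both ways of stopping on that reading: a second SAE in one person, or a fifth affected person. The five-participant trigger alone has probability 0.001 at λ = 0.02 and 0.044 at λ = 0.05. Using it as the whole rule would exaggerate the contrast.

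**The case against.** The best defence is that both clauses have the same form: a number of SAEs, then a number of participants. Read in parallel, the first is repeated SAEs in at least one person and the second is one SAE each in at least five. Under pooling, the mention of one or more participants would add nothing, since every SAE occurs in some participant, and the second clause would add nothing either. This defence has force, and it defeats two stronger inferences that a reader might draw.

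- *That the two clauses cannot both operate.* They can, on the same-participant reading. Even on the pooled reading the second clause is superfluous, not contradictory, because the clauses are joined by OR.
- *That the trial would run on until five participants are affected.* On the same-participant reading, a second SAE in one person stops it earlier. Rules 1 to 3 stop it at two participants with the listed seizure events, rule 4 at one case of status epilepticus or seizure-related hospitalisation, and rule 5 at two suicide attempts or one completed suicide. In addition, unanticipated SAEs are promptly reportable, and the DSMB can vote on continuation and can request interim analyses.

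It is also fair that a DSMB charter exists, was written before data collection, and is not shown. It may define the unit, so it cannot be claimed that the investigators, the DSMB and the IRB would in fact apply different rules. Whether the count runs per phase or across both phases is a detail that a condensed article may leave to the full protocol or the charter.

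The ambiguity itself remains. The parallel reading is an inference from style. The plain words also allow the pooled count, and nothing else in the article decides between them. The concern is with a threshold that the article does state, not with something it leaves out.

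**Conclusion.** The point holds as an ambiguity in a stated safety threshold. The readings give different decisions whenever two, three or four participants each have one device-related SAE that rules 1 to 5 do not catch. One reading has already stopped the trial; the other has not triggered rule 6.

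With 40 active participants, the probability of stopping under rule 6 is about 0.19 against 0.009 at an assumed 0.02 SAEs per participant, and 0.59 against 0.09 at 0.05. These figures rest on assumed rates and independent Poisson counts, and they ignore the other stopping rules. They show how far apart the readings are and do not forecast this trial. The divergence in the stopping points needs no assumed rate.

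The documents do not establish which reading was intended, and no view on that is taken here.

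**What to change.** The sponsor and the DSMB should reconcile the two clauses of rule 6 so that each has a distinct trigger, and state whether the first counts device-related SAEs within one participant or across the study. The choice of rule and threshold is theirs. If the charter already defines the unit, it is enough to carry that definition into the protocol.

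The cost is one sentence in the protocol and, if needed, the charter, with the usual approvals for a protocol change. Sample size and data collection do not change.
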